**Fig. 1 Fig1:**
[figure not shown]
GRAPES-trial flowchart. * Patient enrollment is allowed up to 6 h postoperative. IMHN: intramedullary hip nail; DHS: dynamic hip screw; screws: cannulated screws; THA: total hip arthroplasty; HA: hemiarthroplasty; SF-12: Short Form-12; EQ-5D-3L: EuroQol; TUGT: Timed Up and Go Test; DEMMI: De Morton Mobility Index; SPPB: Short Physical Performance battery

### Standard care

On arrival at the accident and emergency (A&E) department patients receive acetaminophen intravenously, diclofenac (if not contraindicated) and morphine subcutaneously or fentanyl intravenously until numerical rating scale (NRS)-pain scores have dropped below 4. Upon admission the local protocol is started (Table 2). At all centers the 'as needed' medication is administered when the NRS-pain score is 4 or higher and no excessive (opioid-induced) sedation is present. Patients who are deemed able are given intravenous patient controlled analgesia (PCA) pumps with morphine (Table 2). In patients older than 70 years the bolus setting is reduced by 50 %. Preferably patients are operated on using spinal anesthesia. In order to put the patient in an upright position for spinal anesthesia administration femoral blocking with short-acting analgesics can be used. All centers use bupivacaine 0.5 % between 2.0 and 3.0 ml administered at the lumbar level. Additional (long acting) analgesics administered during surgery are noted. The participating centers adhere to the Dutch national guidelines for surgical technique for the various fracture types [43]. Postoperatively, on the day of surgery or the first postoperative day physical therapy is commenced once or twice daily. Physical therapy sessions are usually 30 min long. In the period in which the focus of this study lies physical therapy focuses on strengthening of quadriceps and gluteal musculature, walking and making transfers.

**Table 1 Tab1:** Criteria for participants in the trial

Inclusion criteria	Exclusion criteria
* Intra or extracapsular proximal femur fracture	* Fractures at multiple foci
	* Open fracture/wounds^a^
* Aged 18 years and over	* Acetabular fracture
* Informed consent or proxy consent	* (Suspicion of) concomitant malignancy
	* BMI > 40
	* Unwilling to give proxy consent
	* Preoperative osteosynthesis materials in situ in the ipsilateral leg above knee level
	* Morphine allergy or dependence
	* ASA ≥ 4
	* Cryoglobulinemia
	* M. Raynaud
	* Central neuromuscular disorder
	* Absent ADP/ATP pulsations in the injured extremity
	* Active deep vein thrombosis
	* Suspected pulmonary embolism
	* Patient delay > 24 h
	* NYHA-class ≥ 3
	* IQ-CODE score ≥ 4.6*
	* Long-acting femoral blocks
	* Use of LIA
	* Postoperative HD-instability

^a^Open wounds unable to close per primam, * The IQ-CODE is only administered if the clinician has doubts about the cognitive status of the intented participant

*BMI* body mass index, *ASA* American Society of Anesthesiologists, *ADP* dorsal pedal artery, *ATP* posterior tibial artery, *NYHA* New York Heart Association, *IQ-CODE* Informant Questionnaire for the Cognitive Decline in the Elderly, *LIA* local infiltration anesthesia, *HD* hemodynamic

**Table 2 Tab2:** Hospital protocols

		Analgesic protocol				
Hospital	Thrombosis prophylaxis	Standard		As needed		
Spaarne Gasthuis, Hoofddorp	Fraxiparine 2850 IU 1x^a^	Acetaminophen 1000 mg 4x	Diclofenac 50 mg 3x^b^	PCA-iv morphine	*or*	Morphine 10 mg 6x sc^c^ *or* Oramorph 10 mg 6x^c^
				*If considered able*		
Noordwest Ziekenhuisgroep	Fraxiparine 2850 IU 1x^a^	Acetaminophen 1000 mg 4x	Diclofenac 50 mg 3x^b^	PCA-iv morphine	*or*	Morphine 10 mg 6x sc^c^ *or* Oxycodone 10 mg 6x^c^
				*If considered able*		
VU University medical center	Fraxiparine 2850 IU 1x^a^	Acetaminophen 1000 mg 4x	Diclofenac 50 mg 3x^b^	Morphine 10 mg 6x sc^c^	*or*	Oxycodone 10 mg 6x^c^
Spaarne Gasthuis, Haarlem	Fraxiparine 2850 IU 1x^a^	Acetaminophen 1000 mg 4x	Diclofenac 50 mg 3x *or* 75 mg iv 2x^b^	Morphine 10 mg 6x sc^c^	*or*	Oxycodone 10 mg 6x^c^
Amstelland Hospital	Enoxaparine 40 mg 1x	Acetaminophen 1000 mg 3x	Diclofenac 75 mg im/iv 2x^b^	PCA-iv morphine	*or*	Piritramide 10 mg 6x sc^c^ *or* Tramadol 50 mg 3x
				*If considered able*		

Reported dosages are dosages given in 24 h

*im* intramuscular, *iv* intravenous, *sc* subcutaneous, *PCA* patient controlled analgesia

^a^Dosage is doubled in patients weighing > 80 kg

^b^If no contraindications exist. ^c^: Dosage is reduced by 50 % in patients aged ≥ 70 years

### Study apparatus and treatment schedule

Continuous-flow cryocompression therapy is applied by using the ‘Game Ready system’ (GRS; CoolSystems Alameda, California). Through an anatomically designed hip/groin wrap covering most of the thigh and pelvis up to the iliac crest, the GRS simultaneously delivers both adjustable continuous-flow cryotherapy and intermittent compression through a portable control unit filled with ice and water. The machine has four pressure settings: no pressure, low pressure (5–15 mm Hg), medium pressure (5–50 mm Hg) and high pressure (5–75 mm Hg). Temperature can be adjusted between 4 and 13 °C and is indicated by one, two or three snowflakes. The lowest temperature is started and maintained throughout the study if feasible. Pressure is started at ‘low’ and is increased one step per 4 treatments (Table 3). Depending on the end of surgery patients will be categorized in three treatment schedules with respective start and end-times (Table 3). If patients are uncomfortable the appropriate adjunct will be adjusted stepwise until a comfortable setting is reached, deviations are noted. Adjustments are recorded and comfortable settings are maintained according to the discomfort flowchart (Fig. 2). Patients will be treated between 10 and 12 times during the first 72 postoperative hours, each cycle lasting 30 min. Preferably, treatment cycles and control measurements during the first 72 postoperative hours are performed at fixed moments: 8:00 h, 12:00 h, 16:30 h, and 21:30 h. The GRS-wrap is only in place when CFC therapy is administered and applied/removed by the nurse.

**Table 3 Tab3:** Treatment schedule and pressure settings

End time surgery	Schedule	Start time										
10:00 – 16:00 h	*A*	16:30 h										
16:00 – 21:00 h	*B*	21:30 h										
>21:00 h	*C*	8:00 h										
Cycle no. →	1	2	3	4	5	6	7	8	9	10	11	12
OK + 0	*A:* – Low	*A* – Low										
	*B: –* Low	-										
	-	-										
OK + 1	-	*-*	*A* – Low	*A* – Low	*A* – Med	*A* – Med						
	-	*B –* Low	*B –* Low	*B –* Low	*B –* Med	-						
	*C* – Low	*C* – Low	C – Low	*C* – Low	-	-						
OK + 2					*-*	*-*	*A* – Med	*A* – Med	*A –* High	*A –* High		
					*-*	*B –* Med	*B –* Med	*B –* Med	*B* – High	-		
					*C –* Med	*C –* Med	*C –* Med	*C –* Med	-	-		
OK + 3									-	*-*	*A –* High	*A –* High
									-	*B* – High	*B* – High	*B* – High
									*C –* High	*C –* High	*C –* High	*C –* High

Regular treatment times: 8:00 h; 12:00 h; 16:30 h; 21:30 h

**Table 4 Tab4:** Outcome assessment points

		Assessment point						
Item	Data collection instrument (unit)	Baseline (A&E department)	Day of surgery	24 h	48 h	72 h	Discharge	6 - 8 weeks (outpatient clinic visit)
Demographics	-	X						
Pre-fracture functional status	NMS, KATZ-ADL	X						X
Delirium risk assessment	DRAS	X						
Cognitive function	IQ-CODE	X						
	MMSE						X	X
Blood loss	Intraoperative loss *(cc’s)*		X					
	Drain output^a^ *(cc’s)*			X	X	X	X	
Outcome								
Pain	NRS	X	X	X	X	X	X	X
Analgesics	Acetaminophen	X				X	X	
	NSAID’s	X				X	X	
	Morphine	X				X	X	
Blood loss	Hemoglobin (mmol/l)	X		X		X		
Transfusion incidence	Number of units						X	X
Delirium	DOS-score	X	X	X	X	X	X	
	DRS-R-98^c^		X	X	X	X	X	
	Pyschotropic medication	X				X	X	
Length of stay^b^	*(Hours)*						X	
Functional outcome	TUGT						X	X
	DEMMI							X
	SPPB							X
	Rehabilitation location						X	X
	Rehabilitation duration						X	X
PROM	EQ-5D-3L							X
	SF-12							X
	Satisfaction questionnaire						X	
Complications	General						X	X
	Therapy related						X	X
Feasibility	Nurse staff questionnaire						At discharge of last patient	

*A&E* accident and emergency, *NMS* New Mobility Score, *IQCODE-N* Informant Questionnaire on the Cognitive Decline in Elderly patients, *MMSE* Mini Mental State Exam, *NRS* numeric rating scale, *PC* packed cells, *DOS* Delirium Observation Screening, *DRS-R-98* Delirium Rating Scale Revised 98, *TUGT* Timed Up and Go Test, *DEMMI* De Morton Mobility Index, *EQ-5D-3*
*L* EuroQol questionnaire, *SF-12* Short Form-12 questionnaire

^a^Including autologous reinfusion. ^b^Start count at admission and at the end of surgery. ^c^: administered when DOS ≥ 3

**Fig. 2 Fig2:**
[figure not shown]
Discomfort flowchart. * If a patient reports discomfort for the second time at the same setting this setting is permanently reduced to the setting deemed comfortable

### Co-interventions

In case of discomfort the appropriate adjunct is adjusted accordingly (Fig. 2) and supplemental analgesics are given as needed (Table 2). In both the intervention group receiving CFC therapy and in the control group no restrictions are made towards regularly used static compressive bandages and/or wound drains (with or without autologous re-infusion). Geriatricians are consulted in a standard fashion in patients aged 70 years and over.

### Admission

Patient demographic data are noted on admission as well as American Society of Anesthesiologists (ASA) class, current NRS-pain, delirium observation screening (DOS)-score, activities of daily living (ADL)-Katz score and the New Mobility Score (NMS; Table 4) [44–46]. Time of injury and arrival at the A&E department is noted. Patient delay intervals longer than 6 h are actively explored and reasons for delay are clarified e.g. if a patient was prone and unable to call emergency services.

A standard preoperative venous blood sample is taken in which hemoglobin, hematocrit and mean corpuscular volumes values are measured (Table 4). Upon admission the local hospital analgesic and antithrombotic protocol is started (Table 2). A geriatrician is consulted preoperatively in patients who are older than 70 years and will focus on: polypharmacy, risk reduction of falls, prevention and/or treatment of delirium, optimization of nutritional status. The ADL-Katz score and delirium risk assessment score (DRAS) [47] are completed upon admission; furthermore precipitating factors for delirium (bladder infection and/or retention, fixation, sleep deprivation, electrolyte abnormalities including renal function impairment) are noted throughout the hospital stay. After the operation the surgeon notes the intraoperative blood loss, the type of implant, if applicable intraoperative complications, randomizes the patient and determines the patient’s treatment schedule.

### Cryocompression therapy and clinical measurements

Intervention patients start with CFC therapy 6 h postoperative, until 72 h postoperatively. A trained ward nurse will conduct the pain assessments when the patient is in bed or stationary in a chair for at least five minutes. Directly before and directly after CFC therapy vital signs including NRS-pain are measured by the ward nurse, when the patient is prone in bed for at least five minutes before commencing and five minutes after cessation of CFC therapy. In control patients only NRS-pain is measured at the same time as intervention patients would normally be assessed. All pain measurements are continued throughout the first postoperative 72 h for control and intervention patients alike (Table 4). Three times daily DOS-scores [48] will be obtained; in case of a DOS-score higher or equal to three, geriatricians diagnose and subsequently monitor delirium severity with the delirium rating scale revised 1998 (DRS-R-98) [49] on a daily basis or until the score drops below 12.25 out of 39 (Table 4). Time and amount of administered (psychotropic) medication will be documented. The nurse and ward doctor inspect the wound and dressing in accordance with routine care. Blood samples are taken at postoperative day one and three, and post-transfusion if applicable (Table 4). The timed up and go test (TUGT) is performed before discharge (Table 4). The TUGT will be administered in all patients who are able. If no weight bearing is allowed or patients are physically unable, than the test will be postponed to the outpatient visit. The mini mental state examination (MMSE) is administered for data stratification purposes [50–52], if patients are delirious during admission the MMSE is postponed to the outpatient visit.

In order to document experiences with CFC therapy all treatment patients will fill in a questionnaire at discharge, which is specifically drafted for this study (Table 5). During the study a booklet will be made available into which staff can write down prevalent occurring technical GRS-related problems.

**Table 5 Tab5:** Patient questionnaire

1. Did you feel that the pain reduced when treated with cryocompression therapy?	A	B	C	D	E
2. Would you rather have cryocompression treatment than analgesic pain treatment?	A	B	C	D	E
3. The standard setting used was the coldest; did you like this temperature setting?	A	B	C	D	E
4. Did you request the temperature setting to be upped?	Y				N
5. Did you like the dynamic pressure adjunct?	A	B	C	D	E
6. The pressure adjunct was elevated every 4 treatments, was the pace to fast?	A	B	C	D	E
7. After treatment the muscles are cooled, did this hinder you in moving around outside of bed?	A	B	C	D	E
8. Would you have liked to be treated more often per day than 4 times?	A	B	C	D	E
9. Would you have liked to be treated longer than 30 min per cycle?	A	B	C	D	E
10. Would you have liked to be treated longer than the first 72 h postoperative?	A	B	C	D	E
11. Did you feel like you recovered faster with cryocompression therapy?	A	B	C	D	E
12. Would you recommend the use of cryocompression therapy to other patients?	A	B	C	D	E
13. Can you briefly describe what you think are advantages of cryocompression therapy?	Open text				
14. Can you briefly describe what you think are disadvantages of cryocompression therapy?	Open text				
15. From 0 – 10 how would you rate the cryocompression treatments in general?	(0-10)				

A: agree completely; B: agree; C: neutral; D: disagree; E: disagree completely

Y: yes; N: no

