### Randomization

A balanced 1:1 block (size six) randomization stratified by center will be performed directly after surgery, using Research Manager (RM; version 4.5.0.1), a web-based computer program (Fig. 1). A research nurse who is not involved in the study generates the allocation sequence with RM. Intramedullary hip nail (IMHN), dynamic hip screw (DHS) and cannulated screws are grouped for block randomization, as are total hip arthroplasty (THA) and hemiarthroplasty (HA). The intervention group ‘A’ will receive CFC therapy postoperative; the control group ‘B’ will receive standard care. Due to the nature of the study no blinding can exist as patients, family and physicians notice the use and settings of CFC therapy. Physicians randomize participants with a digital logon to the web-based system or the physician can contact the coordinating investigator and he will randomize the included participant (see Table 1 for criteria).The Informant Questionnaire for the Cognitive Decline in the Elderly (IQ-CODE) questionnaire is administered when the clinician has doubts about the cognitive state that may compromise CFC therapy sessions or study measurements (Table 1). Ideally a MMSE would be used for this purpose, however due frequently perceived pain at the accident and emergency A&E department and consequently administered narcotic analgesics, the hetero anamnestic IQ-CODE is used instead. The coordinating investigator contacts the participating hospitals on a daily basis by telephone or physically to ensure adequate and appropriate enrollment of participants and completeness of data. A list of excluded patients will be drafted.

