## Outcome parameters

### NRS-pain (primary)

The verbally administered 11-point (range 0–10) NRS-pain is a widely accepted assessment tool and has been validated in many different conditions, among is acute pain in the emergency department [53–55]. Reliability and validity has been thoroughly studied in (cognitively impaired) elderly and has shown to maintain acceptable clinometric characteristics [56–58]. NRS-pain scores are compared within the intervention group i.e. pre and post-treatment and compared between the intervention and control groups. Cumulated pain scores will be calculated for both groups by adding the (post-treatment) pain scores of the first 72 postoperative hours.

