## Statistics

### Analysis of outcome parameters

All statistical analyses will be computed using the SPSS statistical package (IMB SPSS, Inc., Release 20.0.0.0, 64-bit edition). Statistical analysis will be performed according to the intention-to-treat principle. Baseline characteristics will be described in accordance with CONSORT guidelines [41] using means and standard deviation in case of normal distribution, and medians and interquartile ranges otherwise. Continuous variables will be checked for normality, visually and by using the Shapiro Wilk test. Our primary analysis focuses on the differences in NRS-pain scores between the study groups 24 h postoperative and will be analyzed by use of Student’s T or Mann–Whitney U tests in case of skewed distribution. To assess treatment effect over time, a mixed model analysis for repeated measures will be performed. This model allows missing data and adjustment for serious confounders and interactions. In case of skewed distributions and outliers non-parametric variants will be used (e.g. Mann Whitney U or Friedman tests). Secondary continuous outcome measures (EQ-5D-3L, SF-12, DRS-R-98 and hemoglobin) will be compared by use of Student’s t or Mann Whitney U tests. Ordinal variables will be analyzed using the Mann–Whitney test. Chi-squared tests will be performed in case of categorical variables. In case of important confounding, analysis will be adjusted to correct for these factors (by use of multiple regression analysis, linear or logistic). A *p*-value of < 0.05 will be considered statistically significant.

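### Pain scores around CFC sessions must be taken lying in bed, while controls may be scored in bed or a chair, so measurement conditions can differ by arm

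*Protocol article*

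**What the plan says.** All references are to the Protocol article. The section Cryocompression therapy and clinical measurements gives three rules in close succession:

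- A general rule that names no arm: "A trained ward nurse will conduct the pain assessments when the patient is in bed or stationary in a chair for at least five minutes".
- A rule for readings directly before and after a CFC session, which are taken "when the patient is prone in bed for at least five minutes before commencing and five minutes after cessation of CFC therapy".
- A rule for controls: "In control patients only NRS-pain is measured at the same time as intervention patients would normally be assessed".

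The section Study apparatus and treatment schedule says that "treatment cycles and control measurements during the first 72 postoperative hours are performed at fixed moments" (8:00, 12:00, 16:30 and 21:30 h), with "each cycle lasting 30 min".

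On use of the scores, NRS-pain (primary) states: "Cumulated pain scores will be calculated for both groups by adding the (post-treatment) pain scores of the first 72 postoperative hours". Analysis of outcome parameters states: "Our primary analysis focuses on the differences in NRS-pain scores between the study groups 24 h postoperative". Table 4 lists NRS at 24, 48 and 72 h without saying whether those readings are tied to a session. On masking, the section Randomization states: "Due to the nature of the study no blinding can exist".

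**The concern.** Pain is a subjective outcome, scored here without blinding, so the conditions of scoring should be the same in both arms. As written they need not be. Session-linked CFC scores are confined to patients lying in bed. Control scores fall under the general rule, which also accepts a chair, and nothing clearly carries the bed condition over to them.

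Chair scores are a real possibility within the measurement window. Under Standard care, physical therapy, including walking and transfers, begins on the day of surgery or the day after. Three of the four fixed moments fall in the daytime, and the general rule itself expects that some patients will be in a chair.

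Rest before scoring may differ too, because a CFC patient at a post-session reading has just had a half-hour session.

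Randomization does not balance a difference of this kind, because it arises after allocation and is linked to the arm. If posture or rest affects the score, part of the between-arm difference would reflect how pain was measured and not what CFC did.

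**Working it through.** **1. Conditions side by side**

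| | CFC, session-linked score | Control score |
|---|---|---|
| Posture | bed only | bed or chair (general rule) |
| Required rest before the score | 5 min before the session; 5 min after it | 5 min |
| Time in bed at a post-session score | 5 + 30 + 5 = 40 min, if the patient stays in bed during the session | at least 5 min at rest, bed or chair |
| Timing | fixed moments | matched to the CFC arm |

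**2. Where the scores go**

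The cumulated 72 h score is built from post-treatment readings, so the bed-only readings enter it directly. For the 24 h comparison the link is conditional. If the 24 h value is a pre- or post-session reading, the bed-only rule applies to the CFC arm. If it is a separate reading, the common bed-or-chair rule covers both arms.

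**3. The plan's sample size**

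Inputs from Sample size calculation: difference 1.3, SD 2.2, alpha 5% (taken as two-sided), power 90%, dropout 22.3%. A two-sample t test needs 61.16, so 62 per arm and 124 in total. Then 124 / (1 − 0.223) = 160, which is the stated figure. Nothing in this point disputes it.

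**4. Size of a possible bias**

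The documents give neither the share of control scores taken in a chair nor the effect of sitting still, compared with lying, on NRS. Both are assumed here.

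- Bias = chair share × posture effect.
- Standard error with 62 evaluable per arm: 2.2 × √(2/62) = 0.395.
- Two-sided rejection rate with no true CFC effect (normal approximation): Φ(bias/0.395 − 1.96) + Φ(−bias/0.395 − 1.96).

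| Assumed chair share | Assumed posture effect | Bias (points) | Share of 1.3 | Rejection rate |
|---|---|---|---|---|
| any | 0 | 0 | 0% | 5% |
| 10% | 0.5 | 0.05 | 4% | 5.2% |
| 40% | 0.5 | 0.20 | 15% | 8.0% |
| 25% | 1.0 | 0.25 | 19% | 9.7% |
| 40% | 1.0 | 0.40 | 31% | 17% |

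Check of the last row: 0.40/0.395 = 1.01, and the two tail terms sum to 0.173.

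**The case against.** The strongest reply is that the text permits a difference without requiring one. Bed satisfies both rules, both require at least five minutes at rest, and every control could in fact be scored in bed. A reader might infer that controls will often be sitting. No section gives the share of scores taken in a chair, and therapy sessions of about 30 minutes once or twice a day do not establish it. This stands.

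The control sentence can also be read differently. It follows a sentence on vital signs including pain, so its limiting word may mean only that controls skip the other vital signs, with the bed condition carried over. That reading is reasonable, but the text does not settle it, and nurses at five sites need an instruction that cannot be read two ways.

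A reader might further infer that the asymmetry favours CFC. No section says that a patient sitting still reports more pain than one lying down. The Discussion mentions greater dynamic pain after some fixation procedures, but both scoring rules concern a patient at rest. A shift towards CFC is plausible and not shown.

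Nor does it follow that every possible 24 h score is affected, since a separate 24 h reading would fall under the common rule.

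It might also be said that the bias cannot be removed in analysis because posture goes unrecorded. The article mentions no such recording, but the CRF is not shown, so this cannot be asserted.

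On size, the result follows the assumptions. Taking 75% of control scores in a chair and a 1.5-point effect would give 1.125 points and a rejection rate of 81%. The documents support that no better than they support zero.

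On rest, the 30-minute session belongs to the treatment as delivered, so some would count the rest it brings as part of the effect. That is arguable. It does not apply to the difference in posture.

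**Conclusion.** The point holds as an arm-linked asymmetry in the stated measurement conditions. It is not a demonstrated bias. The article itself sets a stricter posture for session-linked CFC scores than the one that clearly covers controls, and post-session scores follow about 40 minutes in bed, on the assumption that the patient stays there during the session. These scores feed the cumulated 72 h score with certainty, and the 24 h primary contrast only if the 24 h value is session-linked.

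The effect on the comparison is plausibly towards CFC, but direction and size are undetermined. Under the assumptions tabulated above it ranges from negligible to about a third of the 1.3-point relevant difference, and it vanishes if posture has no effect on NRS. The use of *prone* in the bed rule appears to mean lying down and carries no weight here.

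**What to change.** In Cryocompression therapy and clinical measurements, replace the separate rules with a single condition for study NRS scores: the same posture and the same minimum rest period in both arms at the matched fixed times. Tick posture on the CRF for any score taken otherwise. It would also help to state whether the 24 h value is a pre-session, post-session or separate reading, since that decides whether the primary contrast is exposed.

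Do not add a comparison restricted to scores taken in bed. If session-linked CFC scores are all taken in bed, the restriction would discard only control scores, and it would select controls on a state that arises after randomization and may itself be related to pain or mobility.

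The cost is one sentence in the nurse instruction and one tick box; the sample size of 160 is unaffected. The downside is that, if the common posture is in bed, some control patients may need to be settled there shortly before scoring, and that move could itself influence the score. The minimum rest period should be set with this in mind.
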